**Inclusion criteria:**

• Age between 18 and 35 years old.

• Have no clinical psychiatric diagnosis (schizophrenia, major depression, bipolar disorder, social anxiety disorder).

• Do not use psychotropic, beta-blocker or anti-inflammatory drugs at the time of the study.

• Have no prior experience with mindfulness-based practices.

• Sign the written consent

**Exclusion Criteria**

• Absence of one day of the study

• Have an infectious disease during the study

• Body mass index (BMI) above 30.

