**3. Materials and Methods**

Participants

Fifty young adults of both sexes, aged between 18-35 years will be recruited through wide dissemination on the campus of the Federal University of Rio Grande do Norte-UFRN. The sample size was determined with G * Power of the F test family (RM-ANOVA with intra-between interaction), considering a moderate to high effect size (f = 0.3) at α = 0.05 and 80% of power, as well as 60% correlation between repeated measures and considering loss of participants during the study being necessary at least 40 participants to attend these parameters.

Participants will be interviewed in advance and will complete a series of questionnaires to verify their eligibility for the study. Upon being elected to the study, they will be randomized into two groups proposed in this study.

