**Training**

Based on previous studies, a brief intervention will be performed for 3 days for 30 minutes a day, involving practices contained in the mindfulness program for stress reduction. The exercise used in the study will be a practice of attention focused on the sensations of breathing that will be recorded by a qualified professional. The participant will come to the laboratory during the morning for 3 consecutive days and must stay in a room dedicated to practices throughout the procedure. The control group will spend the same time in a room designated for the study and will be subjected to a task of coloring figures during the same time as the experimental group. The study steps are specified in the diagram below:

Figure 1: Timeline of assessments throughout the study of groups 1 and 2. EEG: Electroencephalography.

In a schematic way, the evaluation with the EEG will be carried out as follows:

Figure 2: Schematic showing the activities to be performed during data acquisition using electroencephalography (EEG).

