**Dosage of salivary cortisol**

Salivary cortisol dosages will be performed from samples collected on day 3 of the protocol. They will be made using commercial dosage kits from the company DRG Instruments GmbH (Germany).

The basic principle used by the kit is the competition ELISA, in which a microplate is sensitized with monoclonal antibodies (IgG) to cortisol. The reading of samples will be performed by spectrophotometry.

On day 1 of the protocol, the participant will answer the pre-intervention questionnaires and a blood sample will be collected for subsequent analysis of cortisol and BDNF.

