**Statistical analysis**

Initially, Kolgomorov-Smirnov normality tests will be applied to determine if the data obey a normal distribution. Once this prerequisite is met, Student's t test (parametric variables) or Mann Whitney U test (non-parametric variables) will be applied to detect the occurrence of significant differences within group and ANOVA to evaluate between groups differences. Spearman's correlation test will also be applied to test the occurrence of correlations between variables (anxiety, affect, stress and mindfulness, trait and state).

An exploratory and confirmatory factor analysis will be performed to verify the domains and association between the factors existing in the questionnaires. The internal consistency of the factors will be verified using Crombach's Alpha and only saturation values ​​greater than 0.4 for the eigenvalues ​​will be computed for the item's participation in the investigated domain.

For the analysis of plasmatic and behavioral markers, correlation tests and multivariate analysis will be used.

For all tests, the significance level (p value) less than or equal to 0.05 will be considered.

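### Two of the three exclusion criteria, absence on a study day and infection during the study, can be met after randomisation, so as written they remove randomised participants from the comparison.

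*Protocol*

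**What the plan says.** In the protocol's Materials and Methods (Participants), eligibility is settled first: "Participants will be interviewed in advance and will complete a series of questionnaires to verify their eligibility for the study". Allocation follows: "Upon being elected to the study, they will be randomized into two groups proposed in this study". The Training section then sets the schedule: "The participant will come to the laboratory during the morning for 3 consecutive days". The main stress-response measure comes at the end: "Salivary cortisol dosages will be performed from samples collected on day 3 of the protocol".

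The Exclusion Criteria list three items. One is a body mass index limit, which can be checked at screening. The other two are "Absence of one day of the study" and "Have an infectious disease during the study".

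The Statistical analysis section plans "ANOVA to evaluate between groups differences". Nothing in the protocol says that a participant who meets one of these two criteria after allocation stays in follow-up or is analysed in the assigned arm.

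**The concern.** An exclusion criterion decides who may enter a trial. These two describe things that can happen to people who have already entered and been allocated. Applied as written, they turn a comparison of the groups formed by randomisation into a comparison of those in each group who attended every day and stayed free of infection.

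Randomisation makes the arms comparable at allocation. It does not make the remaining subsets comparable. The arms do different things for 30 minutes a day (breathing attention or colouring), so attendance could differ between them. Attendance could also be related to stress, anxiety or affect, all of which are outcomes. If both hold, the contrast is biased. Separately, outcomes that could have been measured are lost.

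**Working it through.** **Step 1: can each criterion be judged before randomisation?**

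| Event | Judged before randomisation? | What remains obtainable |
|---|---|---|
| BMI above 30 | Yes | Not applicable |
| Infection present at screening | Yes | Not applicable |
| Absence on day 1 | Cannot be told: the timeline figure is not shown | Day-1 questionnaires and blood sample are lost |
| Absence on day 2 | No | Day-1 baseline and day-3 outcomes |
| Absence on day 3 | No | Day-1 data; day-3 salivary cortisol is lost |
| Infection arising during the study | No | Depends on timing |

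At least three of these situations fall after allocation. Only the day-2 absence clearly leaves both baseline and day-3 data within reach.

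**Step 2: formula for the shift.** The protocol gives no figure on this point, so there is none to reproduce. Let *p* be the fraction of an arm removed and *g* the mean of the removed minus the mean of the retained, in SD. The full-arm mean is (1 − *p*) × retained mean + *p* × removed mean, so

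retained mean − full-arm mean = −*p* × *g*.

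The shift in the contrast between arms 1 and 0 is −(*p*₁*g*₁ − *p*₀*g*₀). It is zero when *p* × *g* is the same in both arms.

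**Step 3: size on assumed values.** Assumptions: 50 recruited and split equally, 25 per arm (the allocation ratio is not stated); *g* between 0.5 and 1.0 SD; removal from one arm only.

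- 5 of 25 removed: 5/25 × 0.5 = 0.10 SD; 5/25 × 1.0 = 0.20 SD.
- 2 of 25 removed: 2/25 × 0.5 = 0.04 SD; 2/25 × 1.0 = 0.08 SD.
- Same fraction and same gap in both arms: 0.

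**Step 4: cross-check with a selection model.** Assume no true effect, a standardised outcome, and removal of those highest on a latent variable that correlates *r* = 0.3 to 0.5 with the outcome. With φ the standard normal density, *z* the (1 − *q*) normal quantile and *q* the fraction removed, the retained mean is −*r* × φ(*z*)/(1 − *q*). For *q* = 0.2 this is −*r* × 0.28/0.8 = −0.35*r*; for *q* = 0.1 it is −*r* × 0.1755/0.9 = −0.195*r*. The type I error uses a normal approximation with SE = √(1/*n*₁ + 1/*n*₀) for the retained numbers.

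| Removed, arm 1 v arm 0 | Size of shift (SD) | Two-sided type I error |
|---|---|---|
| 10% v 10% | 0 | 5.0% |
| 20% v 10% | 0.05 to 0.08 | 5.3% to 5.7% |
| 20% v 0% | 0.11 to 0.18 | 6.4% to 9.0% |

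For 20% v 0% and *r* = 0.5, for example: shift 0.35 × 0.5 = 0.175, SE = √(1/20 + 1/25) = 0.30, ratio 0.58, type I error 9.0%. Steps 3 and 4 agree in order of magnitude.

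**The case against.** **The protocol does not define exclusion.** It could mean stopping the sessions, stopping data collection or deletion from the analysis, and an analysis plan that is not shown could define an as-randomised set. This stands as a limit on certainty. It does not remove the point. The criticism is of a rule the protocol does state, not of a missing analysis population. Removal is the natural reading of an exclusion criterion, and no later plan can recover day-3 outcomes that were never collected.

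**The rules have a scientific purpose.** The objective concerns three days of practice in healthy people, with cortisol among the outcomes, so full exposure and freedom from infection are reasonable conditions to examine. This stands, and it is why that subset should be kept as a sensitivity analysis.

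**Nothing shows that removal differs by arm.** Both groups spend the same time in a laboratory room, and infection has no evident link to allocation. This also stands: the bias is possible, not demonstrated.

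A reader might go further than the documents allow in four ways:

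- That the result will be tilted towards mindfulness. The direction cannot be found from the document.
- That the plan accepts a 20% loss, because (50 − 40)/50 = 0.20. No loss rate is stated, and the wording can be read as 40 already including loss.
- That the shift is a third of the planned effect, by turning f = 0.3 into 2 × 0.3 = 0.6 SD. The protocol states "considering a moderate to high effect size (f = 0.3) at α = 0.05 and 80% of power" for a repeated-measures interaction, where that conversion is not straightforward. It names no 0.6 SD effect.
- That all lost data are recoverable. Missing day 1 or day 3 loses measurements at one end.

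**Conclusion.** The point holds. The protocol lists as exclusion criteria one event that must follow randomisation (absence on day 2 or day 3) and one that may (infection during the study). Read naturally, the comparison is then restricted to full attenders without infection.

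The order of events comes directly from the text. That excluded participants leave the analysis is the natural reading but is not spelled out. The bias is conditional on removal that differs by arm and is related to outcome. In the illustrations it runs from nothing, when removal is equal and similar, to 0.10 to 0.20 SD when 5 of 25 are removed from one arm only. Those sizes rest on the assumed gap, the assumed 25 per arm and the assumed imbalance. The avoidable loss of data is clearest for a day-2 absence. Whether randomisation already takes place after the day-1 measures cannot be judged without the timeline figure.

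**What to change.** - Keep under Exclusion Criteria only conditions that can be judged before randomisation. Infection present at screening can remain there.
- Reclassify later absence or infection as protocol deviations or intercurrent events, and state what happens to those participants' data.
- State that participants who miss a session are still asked for the day-3 assessments.
- State that all randomised participants with outcome data are analysed in their assigned arm.
- Report the full-attendance, infection-free set as a sensitivity analysis, particularly for cortisol.

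The choice of missing-data model can be left to the statistical analysis plan. Whether someone with an infection continues the sessions is a separate clinical matter, not addressed here.

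The cost is mainly wording, plus the effort of obtaining day-3 assessments from people who missed a session. The statistical downside is slight dilution of the effect by partial attenders; the sensitivity analysis still shows the result for full attenders. The change should be made before outcomes are lost, because those not collected cannot be restored.

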**Training**

Based on previous studies, a brief intervention will be performed for 3 days for 30 minutes a day, involving practices contained in the mindfulness program for stress reduction. The exercise used in the study will be a practice of attention focused on the sensations of breathing that will be recorded by a qualified professional. The participant will come to the laboratory during the morning for 3 consecutive days and must stay in a room dedicated to practices throughout the procedure. The control group will spend the same time in a room designated for the study and will be subjected to a task of coloring figures during the same time as the experimental group. The study steps are specified in the diagram below:

Figure 1: Timeline of assessments throughout the study of groups 1 and 2. EEG: Electroencephalography.

In a schematic way, the evaluation with the EEG will be carried out as follows:

Figure 2: Schematic showing the activities to be performed during data acquisition using electroencephalography (EEG).

**Stress Induction and Assessment of Emotional Regulation**

The stress test to be used is the Mannheim multicomponent stress test (MMST) (KOLOTYLOVA et al., 2010). The MMST is a multi-component test that involves emotional, auditory, and arithmetic stimulation for 5 minutes. The response of the HPA and SNA axis seems to be like that obtained with the TSST (Trier Social Stress Test), the standard test used to verify the stress response in laboratory studies. (REINHARDT et al., 2012). In the first 3 minutes of the test, the participant is presented with several images with positive, negative, and neutral emotional valences and is asked to categorize the image into these valences on a scale of 1-7. A total of 52 images will be displayed. After that, a white noise ranging from 78-98dB is presented and the participant is asked to perform an arithmetic test according to what appears on the computer screen in front of him. This test is the PASAT (Paced Auditory Serial Addition Test) in which the participant must add the last digit shown to the one immediately before, typing the sum of both digits on the keyboard in front of him.

**Biochemical and physiological assessment**

**Electroencephalography (EEG), Electrocardiogram (ECG) and galvanic skin response (GRS):**

Electroencephalography will be performed with a 64-channel BrainAmp DC device (Brain Products GmbH, Munich, Germany), using ActiCap active electrodes (Brain Products GmbH, Munich, Germany). The ECG and GSR electrodes will be connected to BrainAmp ExG (Brain Products GmbH, Munich, Germany). The EEG data will be analyzed using Matlab software using the EEGLAB toolbox (DELORME; MAKEIG, 2004).

**Saliva:**

Saliva samples will be collected before the start of the stress test and 15, 30 and 60 minutes after its end. The samples will be collected in an appropriate device - Salivettes (Sarstedt, Germany) and later processed, centrifuged at 3000 RPM, for 15 minutes and stored at -30º C until further dosing.

**Dosage of salivary cortisol**

Salivary cortisol dosages will be performed from samples collected on day 3 of the protocol. They will be made using commercial dosage kits from the company DRG Instruments GmbH (Germany).

The basic principle used by the kit is the competition ELISA, in which a microplate is sensitized with monoclonal antibodies (IgG) to cortisol. The reading of samples will be performed by spectrophotometry.

On day 1 of the protocol, the participant will answer the pre-intervention questionnaires and a blood sample will be collected for subsequent analysis of cortisol and BDNF.

**Blood collection:**

Study participants will undergo venipuncture of 20 ml of blood after fasting for 8 hours before and after the intervention proposed in this project. They will be instructed to have a peaceful night's sleep and to attend the collection point at the agreed time. Blood collection will be carried out in the non-dominant arm of each participant, in the morning (between 8:00 and 9:30 am) after 45 minutes of the participant's rest. Peripheral blood samples will be collected without anticoagulant (10 mL) to study the hematological, lipid, hepatic and renal profiles and the endocrine marker (cortisol) and BDNF.

**Dosage of plasma cortisol**

Cortisol levels will be determined in duplicate by the immunoenzymatically method (ELISA). Coefficients of variation will be calculated and must be less than 20%. The basic principle used by the kit is the competition assay, in which a microplate is sensitized with monoclonal antibodies (IgG) to cortisol. Unknown samples (from participants) compete with cortisol linked to a peroxidase enzyme for the cited antibodies. After an incubation period, unbound components are washed away. A substrate (tetramethylbenzidine) is added, and it will oxidize the cortisol-bound enzyme producing a color change. With the addition of a stop solution, another color change occurs and then a spectrophotometric reading will be taken using a filter with an adequate wavelength. It is noteworthy that using this type of ELISA, the higher the optical density, the lower the amount of hormone present in the sample, the opposite being true.

**BDNF dosage**

2mL aliquots of plasma will also be separated after blood collection, for BDNF analysis, through the enzyme immunoassay technique (ELISA), using commercial kits.

**Autonomic Nervous System Assessment**

The measurement of the modulation of the Autonomic Nervous System (ANS) on the heart will be performed using the Heart Rate Variability (HRV) technique that uses the RR intervals of the electrocardiogram (ECG) captured and recorded for one hour with the volunteers in awake with electrodes connected to BrainAmp ExG (Brain Products GmbH, Munich, Germany).

Time and frequency domain measurements (HF (High frequency), LF (Low frequency), VLF (Very low frequency) and Ratio (LF/HF) will be used to represent cardiac vagal activity.

**Interoceptive evaluation**

In addition to applying the scale for interoceptive assessment (MAIA) described above, we will carry out an objective assessment based on previous studies (KOCH; POLLATOS, 2014; SCHANDRY, 1981).

The heartbeat count test will be used to verify the cardiac accuracy that reflects the level of interoceptive sensitivity of the volunteers. This test is widely used in the literature and cardiac interoception is representative of body interoception. The test consists of silent counting without tactile handling of the number of heartbeats perceived during three periods of time 25s, 35s and 45s, which are randomly combined, interspersed by 30s (SCHANDRY, 1981). Thereafter, the perceived number of beats is compared with the actual number of beats, resulting in the level of cardiac accuracy. The counting protocol with the three time periods interspersed by 30s will be repeated three times, and the mean of the two closest cardiac accuracy values ​​will be considered. The repetition of this procedure on different days will be performed to ensure the reproducibility of the level of interoceptive accuracy of the volunteers. Volunteers will be classified as having high and low interoceptive sensitivity based on the sensitivity criterion above or below 75% accuracy, respectively.

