**2. Objectives**

General:

• Assess the impact of a brief training on the stress response, interoception and well-being on healthy individuals.

Specific:

• Verify the relationship between mindfulness trait and hypothalamic-pituitary-adrenal axis reactivity.

• Analyze the neuroendocrine response to a stress event after a brief mindfulness-based intervention.

• Assess the impact of mindfulness practice (3 days) on the attention system, autonomic nervous system, and interoceptive ability.

• Check the influence of the practice on self-report measures of stress, anxiety, and affect

• Assess participants' electroencephalographic activity before and after the proposed intervention, during a sustained attention test, an interoception test, and during the stress test.

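### Scoring heartbeat counting from the two closest of three runs is less precise than averaging all three, and the role of the 75% class should be stated

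*Protocol*

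**What the plan says.** The Protocol, section Interoceptive evaluation, describes silent heartbeat counting over periods of 25, 35 and 45 seconds. This set of periods "will be repeated three times", and the score is "the mean of the two closest cardiac accuracy values". The section gives no reason for leaving one run out.

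It then adds: "Volunteers will be classified as having high and low interoceptive sensitivity based on the sensitivity criterion above or below 75% accuracy, respectively". A value of exactly 75% falls in neither class. The section does not say whether the class or the percentage goes into the comparison of the groups.

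The test is also repeated over days: "The repetition of this procedure on different days will be performed to ensure the reproducibility" of the accuracy level. How the days are combined is not stated.

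The measure serves a named objective. Section 2, Objectives, asks for the effect of three days of practice "on the attention system, autonomic nervous system, and interoceptive ability". The section Statistical analysis says that a "t test (parametric variables) or Mann Whitney U test (non-parametric variables) will be applied", and it adds ANOVA and Spearman correlation. It names no test for a two-class outcome.

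**The concern.** Keeping the two runs that agree looks like protection against a bad run. But with three values, two will often lie close together by chance, and their closeness says little about whether they are near the person's true accuracy. The dropped run is always the one furthest from the other two, so dropping it moves the score by half of that run's distance from the three-run mean. If the run was valid, the shift is added noise.

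At stake is precision on one of the trial's named objectives. The protocol recruits 50 and states a need for at least 40, so there is little precision to spare, and the discarded run has already been recorded. The 75% split raises a second, conditional question: if the class rather than the percentage were analysed, much more information would be lost.

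**Working it through.** The protocol gives no error variance, reliability, share above 75% or power for this test, so there is no stated figure to reproduce. Its inputs are three runs, the closest-pair rule and the 75% cut. Everything else below is an assumption.

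**1. Error variance with independent normal run errors, variance σ² per run.**
- Mean of three: σ²/3 = 0.333σ².
- Two runs fixed in advance: σ²/2 = 0.500σ².
- Two closest: the score equals the three-run mean minus half the dropped run's deviation from it. Its variance is therefore σ²/3 plus a quarter of the expected squared deviation of the most extreme run. For normal errors this gives (1/2 + √3/(4π))σ² = (0.500 + 0.138)σ² = 0.638σ². Simulation of 2,000,000 triplets agrees (0.638).
- Ratio to the mean of three: 0.638/0.333 = 1.92. Two fixed runs: 1.50. Median of three: 1.35.

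**2. Other error shapes (simulated variance relative to the mean of three).**

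| Run errors | Two closest | Median | Median ÷ two closest |
|---|---|---|---|
| Uniform | 2.47 | 1.80 | 0.73 |
| Normal | 1.92 | 1.35 | 0.70 |
| t, 5 df | 1.46 | 1.05 | 0.72 |
| Exponential | 1.35 | 1.08 | 0.80 |
| Laplace | 1.32 | 0.96 | 0.72 |
| 10% of runs at 3×SD | 1.30 | 0.96 | 0.73 |
| t, 3 df | 0.91 | 0.68 | 0.74 |
| 10% of runs at 5×SD | 0.78 | 0.60 | 0.77 |

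The t row with 3 df is unstable in simulation; a second run gave 0.96 for the two closest, so the two scores are about equal there. With 5% of runs at 8×SD the two-closest ratio falls to 0.56. The last column is below 1 in every row.

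**3. Effect on the total variance of the outcome.** Let r be the single-run reliability, so the true share is r and the error share is 1−r. The inflation is [r + 0.638(1−r)] / [r + 0.333(1−r)].
- r = 0.6: (0.6 + 0.255)/(0.6 + 0.133) = 0.855/0.733 = 1.17.
- r = 0.8: (0.8 + 0.128)/(0.8 + 0.067) = 0.928/0.867 = 1.07.
- Wider range: 1.23 at r = 0.5 and 1.03 at r = 0.9.

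In terms of 50 participants, 50/1.07 ≈ 47 and 50/1.17 ≈ 43 would give the same precision with the three-run mean. These figures are for a score taken on one occasion.

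**4. The 75% class, only if it were the analysed variable.** For a normal score with share p above the cut, the efficiency relative to the continuous score is φ(z)²/[p(1−p)], where z is the normal quantile for p.
- p = 0.5: 2/π = 0.637, a loss of 36%. This is the smallest possible loss.
- p = 0.3: 0.576, a loss of 42%.
- p = 0.2: 0.490, a loss of 51%.

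As an illustration, with an assumed standardised difference of 0.8 and the smallest loss, power would go from 72% to 52% with 20 per arm, and from 81% to 62% with 25 per arm.

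**The case against.** **The rule guards against a lapse or a lost count.** This stands in part. Where gross outlier runs are fairly common the two-closest score does beat the mean of three (0.78 with 10% of runs at 5×SD), so it would be wrong to say that the rule never gains. But the protocol gives no sign of how often such runs occur, and the median of three had the lower variance in every shape tried. Outliers are therefore a reason for the median rather than for the closest pair.

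**The factor of 1.9 exaggerates.** A reader might infer that the outcome's variance nearly doubles. It does not: 1.9 applies to run error alone and to roughly normal errors. The effect on total variance is far smaller, and it would shrink further if scores were averaged over days.

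**Skew might bias the scores.** A reader might infer that scores near the ceiling are pushed up enough to mislead. The size depends on an assumed spread: with mean 75%, the bias is +1.6 points for Beta(6,2) runs (within-person SD 14.4 points) but +0.4 for Beta(24,8) (SD 7.5 points). The same rule applies to both arms and occasions, so the bias largely cancels in the randomised comparison.

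**The split discards over a third of the information.** A reader might infer this as fact. The documents do not support it. The section says only that "Volunteers will be classified as having high and low interoceptive sensitivity"; it does not say that the class replaces the percentage in any test, and the tests in Statistical analysis suit a continuous score. The class may be purely descriptive.

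**Importance.** It is also fair that heartbeat counting is one measure among several, alongside the MAIA, and that a rule fixed in advance and applied equally does not threaten type I error.

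**Conclusion.** The scoring rule is a real but moderate weakness. With independent, roughly normal run errors it gives about 1.9 times the error variance of the three-run mean and is worse than two runs chosen in advance. The cost in total variance is about 7% to 17% at assumed single-run reliabilities of 0.8 to 0.6. The direction reverses only if gross outlier runs are fairly common, and the median is then the better score. The issue is lost precision and does not threaten the validity of the comparison.

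The 75% class needs clarifying and is not a demonstrated loss. The figure of at least 36% applies only if the class is the analysed outcome, which the protocol does not state. This loss and the scoring loss arise at different steps and should not be added. The gap at exactly 75% is a small drafting fault that stands in either case.

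**What to change.** In Interoceptive evaluation, replace the closest-pair rule with the mean of all three runs, excluding a run only for an ECG artefact defined in advance. If lapses or lost counts are the main concern, use the median of three instead. State that the continuous accuracy score is the outcome for the group comparison. Keep the 75% class, if wanted, to describe the sample, and define the high class as at or above 75%.

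The cost is two or three sentences in the protocol, with no new data or visits. The one downside of the mean is less protection against an outlier run that the artefact rule does not catch. The median gives that protection at about 1.35 times the error variance of the mean under normal errors, still well below the 1.92 of the present rule. The closest-pair score can still be computed from the same runs if it is wanted for comparison with other studies.
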